**Figure 3 fig3:**
[figure not shown]
Study parameters and flow diagram. @ clinical consult, NYHA, 6MWT. # Echocardiography, ECG, CXR, ESE. *(FBE, EUC, lipids, HbA1c, Ca Mg, Alb, acute phase); UACR, NT-ProBNP. 6MWT, 6-min walk test; BP, blood pressure; eCDSMP, electronic chronic disease self-management programme; CHF, congestive heart failure; COPD, chronic obstructive pulmonary disease; CR, cardiac rehabilitation; CKD, chronic renal impairment; CXR, chest x-ray; DM, diabetes mellitus; EUC, electrolytes and kidney function; ESE, exercise stress echocardiography; ECG, electrocardiography; FBE, full blood examination; HbA1c, glycosylated haemoglobin; HFpEF, heart failure preserved ejection fraction; HFrEF, heart failure reduced ejection fraction; LVEF, left ventricular ejection fraction; MTWT, “Meeting Two Worlds Together”; MLHF, Minnesota living with heart failure; NT-pro-BNP, brain natriuretic peptide; NYHA, New York Heart Association; PACIC, patient assessment of chronic disease capacity; RCT, randomised controlled trial; RHC, right heart catheterisation; TBA, to be advised; UACR, urine albumin creatinine ration; yo, year old.

### Delphi methodology (Phase 3)

5.4.

We aimed to conduct a Delphi Survey through a workshop, including a SCRinHF Trial Focus Group. A series of questionnaires will allow experts to develop ideas on the SCRinHF tool and potential future developments. The process will choose a facilitator, identify experts, define the problem, go through three rounds of questions, and finally act on the findings. The specific question will be formulated after the results of the cohort study are synthesised.

### Study population/ recruitment of subjects / setting

5.5.

The study setting of Western Melbourne defined the catchment although recruitment will only take place at community cardiology outpatients and support services for CHF. Recruitment will occur over a 6-month period. Patients identified will be referred to the study case manager for consent, and thetime will then be arranged to review the CFPI, PHQ-9, MLHF, and PACIC. Baseline demographics, tests, and questionnaire scores (Figure 3) will be recorded. All staff will be healthcare workers within community cardiology and aligned services. Participants will be recruited over a 12-month period, from September 2021 to September 2022, and followed for 12 months, ending September 2023. Health staff from primary and tertiary care managing CHF patients will be approached to complete the ACIC, between September 2021 and September 2022.

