## Background

1.

Congestive heart failure (CHF) causes significant morbidity and mortality. At least 50% of patients have one or more comorbid conditions such as type II diabetes, coronary heart disease, chronic kidney disease, hypertension, and others. Patients diagnosed with CHF take multiple medications and prescribed complex treatment regimens. Good health literacy is needed to action diet, complex self-management skills, and maintain compliance life-long (1, 2). In addition, interacting effectively with health systems is required for lifestyle maintenance, behavioural changes, and consolidation of chronic disease self-management (CDSM). Patients and health system factors can act as barriers to optimal care, including developing new comorbidities, geography (isolation and remoteness), language, culture, education and socio-economic disadvantage, social supports, and negative attitudes towards establishments (3). Hospital readmissions are high, with 25–50% occurring within 1–6 months of discharge; this largest cost contributor is also preventable and amenable, as studies have demonstrated the care process (4). Better healthcare delivery systems could be achieved by the addition of patient self-management capabilities within programmes that meet patient needs and link health services (4, 5).

Chronic disease management and CHF programmes share similar care domains, one aspect is CDSM. Despite setbacks, there is optimism that CDSM will provide increasing importance to CHF programmes. Nevertheless, to an increasing extent, translational issues such as the containment of resource utilisation and cost blowouts must be factored into the aims of CDSM. These are, however, not the primary aims of large randomised controlled trials. These translational issues are better understood when exploring a patient’s journey. When patients seek health services, the acuity determines if interactions are in the community or *via* acute services such as ambulance, emergency, and hospital admissions. Following acute care, patients then transition back to the community. This process creates new information, new members of a health team, and may also create silos. There are CHF patients that inadvertently utilise the acute pathways and are potentially preventable admissions. It is thus vital that CDSM research aligns with clinical and administrative realities.

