## Patient cohort and selection criteria

4.

A minimum of 40 patients with CHF who meet the inclusion criteria will be offered an opportunity to participate. In uncertain cases, subjects will be considered eligible if the review of medical records demonstrates that they have a CHF diagnosis based on ACC/AHA and National Health Data Dictionary standardised definitions (1, 2). The project physicians will perform this. An independent physician will review uncertain cases.

Eligible patients will be: aged over 18 years; able and willing to provide informed consent; started SGLT-2i within 6 months - for systolic HF (echocardiographic EF <40%); receive one aspect of CHF care within a defined study health corridor.Patients will be excluded: If concerns are raised by any medical staff, the patient has a life expectancy of ≤6 months whilst receiving palliative or nursing home care. Cognitive status and dementia will not be a contraindication if there is consent from a caring relative or legal guardian and the ability to complete the CFPI; have a significant neurological/cognitive impairment or are unable for any reason to provide written informed consent; do not usually reside within the region (or for whom no follow-up data can be obtained); started SGLT2-i for more the >6 months.*Health Staff* will be sent surveys if they manage chronic diseases, including CHF and are willing to complete an Assessment of Chronic Illness Care (ACIC) questionnaire.

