### End points

5.9.

The study endpoints for each phase are: Phase 1 – documentation of health journeys of patients; Phase 2 – interrogation of CFPI and SCRinHF tools for self-management capabilities and readmission risks; and Phase 3 – all data will be accumulated and discussed in the Delphi process. The primary endpoint is the readmission risk as scored by CFPI and SCRinHF and the correlation between the two tools. In addition, the following data will be collected: detailed maps of individual patient journeys and a patient and staff questionnaire on the process. Validation and times to complete the short and long forms will be recorded. The primary endpoint is 80% concordance in MACE and medical events between CFPI and SCRinHF tools. Secondary endpoints are data for cost analysis, and to inform the focus group in planning an RCT for efficacy, validity, reliability, and variability.

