### Expected outcomes

5.12.

The primary outcomes are to achieve concordance in readmission risk between CFPI and SCRinHF, and the number of patient readmissions to the hospital. The secondary outcome is to achieve convergent validity between CFPI and SCRinHF and potential economic cost benefits using the SCRinHF tool.

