### Statistical aspects and data analysis

5.15.

The study cohort assesses feasibility, which will allow appropriate parameters to determine sample size power calculations for future studies that will utilise a controlled design. Initial data analysis will investigate the distribution characteristics of each primary and secondary outcome measure and determine either a parametric or semi-parametric statistical approach to main data analysis. A combination of descriptive statistics, linear mixed models, and generalised estimating equations will be used to calculate and present data. If continuous outcome data are approximately normally distributed, then linear mixed models (LMMs) will be used to examine change over time for each measure at intra-and inter-individual levels. If the distribution of outcome data is more amenable to a semi-parametric approach, then we will use generalised estimating equations (GEEs) to calculate an average estimate of the intervention effect for the cohort. Descriptive statistics for baseline demographics and clinical characteristics will be presented as means (standard deviation) for continuous data and count (percent) for categorical data. As an example, the previous publication provides estimates for pilot sample size calculations for categorical data. A future RCT of 200 patients in each arm for effects size of 25% reduction in readmission at 12 months established an event rate of 1,600 readmissions at 12 months (25–50% historical rate at 1 and 6 months), 90% power, and 5% two-sided significance, and 25–75 patients are published recommendations for small to large, standardised effect sizes (30). With the introduction of SGLT-2, the population level effect size is not known, and we have chosen >40 patients with an LVEF <40% and a NYHA class of 2 or 3. The event rates are well documented as 25% for 1-month readmission and 1-year mortality. Follow-up at 12 months predicts >100 admissions and > 10 mortalities. Interim analysis will ensure that this modelling supports the study goals.

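### The observed outcome is readmission, but the cohort is ambulatory with no index admission and a time window starting at SGLT2-i initiation, so the event has two meanings and the admission forecast rests on rates that do not describe this cohort

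*Protocol article*

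**What the plan says.** All references are to the protocol article.

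- **Outcome.** Section 5.12: "The primary outcomes are to achieve concordance in readmission risk between CFPI and SCRinHF, and the number of patient readmissions to the hospital". Section 5.9: "The primary endpoint is the readmission risk as scored by CFPI and SCRinHF and the correlation between the two tools". Section 2.1 lists hospital readmissions among the health outcomes on which the SCRinHF's predictive validity is to be established, and section 3 repeats this over 12 months.
- **Who is enrolled.** Section 4 asks for age over 18, consent, SGLT2-i started within 6 months for heart failure with EF below 40%, and that patients "receive one aspect of CHF care within a defined study health corridor". No prior or recent admission is required. Section 5.5: "recruitment will only take place at community cardiology outpatients and support services for CHF".
- **When counting starts.** Section 5.7 sets the period of interest at 0 to 12 months from SGLT2-i initiation. Section 5.5 has participants followed for 12 months in connection with recruitment. Section 5.8 records subsequent hospitalisation at 6 and 12 months.
- **Rates relied on.** The Background describes readmissions as "25–50% occurring within 1–6 months of discharge". Section 5.15: "The event rates are well documented as 25% for 1-month readmission and 1-year mortality". The same section then predicts more than 100 admissions and more than 10 deaths over 12 months.
- **Baseline data.** Section 5.6 collects recent and prior hospitalisations. No section uses them to define or describe the outcome.

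**The concern.** A readmission presupposes a discharge. Under the stated criteria a site could enrol one patient who has never been in hospital and another discharged the week before. An admission in the first is a first admission, and in the second an early post-discharge readmission. The plan gives both the same name and does not say that they are to be pooled.

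The time window adds a second problem. A patient who started the drug five months before enrolment and was in hospital three months before enrolment has a stay that is both a baseline recent hospitalisation (5.6) and an event inside the period of interest (5.7). If it is counted as an outcome, the tools are credited with, or faulted for, predicting something that had already happened. The raw patient data from which the SCRinHF is completed may even contain it.

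Three results are at stake: predictive validity against observed events, the readmission count in 5.12, and the event forecast in 5.15. The Discussion presents the anticipated event rates as a strength for planning a later randomised study, so the mismatch would carry forward.

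**Working it through.** **1. The time window.** Drug start may precede recruitment by up to 6 months (section 4). A 12-month window from drug start then leaves as little as 12 − 6 = 6 months after recruitment, and up to 6 months of it lies before scoring. I take both tools as scored at baseline. Section 5.5 arranges the CFPI review after consent; the visible text does not date the SCRinHF.

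**2. Reproducing the plan's forecast.** Inputs from section 5.15: N just above 40 (40 used here), 25% one-month readmission, 25% one-year mortality.

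- Deaths: 40 × 0.25 = 10. This matches more than 10 for N slightly above 40.
- Admissions, one-month rate applied every month: 40 × 0.25 × 12 = 120.
- The same, allowing for deaths: mortality hazard −ln(0.75) = 0.288 per year; mean follow-up 0.25 / 0.288 = 0.869 years; 40 × 0.869 × 12 × 0.25 = 104.

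Both admission figures satisfy more than 100. Other readings of the plan's rates do not:

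- 50% per 6 months, as a count: 40 × 0.5 × 2 = 40.
- 50% per 6 months, as a hazard: 40 × 0.693 × 2 = 55.
- 25% per 6 months: 40 × 0.25 × 2 = 20.
- 25% in one month, counted once: 40 × 0.25 = 10.

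Of the readings tried, the forecast is reached only if every patient carries the one-month rate in all 12 months, that is, 0.25 × 12 = 3 admissions per patient-year.

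**3. What an ambulatory mix would give.** The document states neither the share f of patients with a recent index admission nor the annual admission rate r in the others. Both are assumptions here. Ignoring deaths, expected admissions = 40 × [3f + (1 − f) r].

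| f | r = 0.25 | r = 0.5 | r = 1.0 |
|---|---|---|---|
| 1 | 120 | 120 | 120 |
| 0.75 | 92.5 | 95 | 100 |
| 0.5 | 65 | 70 | 80 |
| 0.25 | 37.5 | 45 | 60 |
| 0 | 10 | 20 | 40 |

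This is generous to the plan, because it keeps recently admitted patients at the one-month rate all year. If only the first month after an index discharge is counted, the figure is 40 × f × 0.25, or 2.5 to 10 for f from 0.25 to 1.

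**4. What is not touched.** Agreement between CFPI and SCRinHF risk classifications needs two scores per patient and no event, so it can be computed in all 40 whatever their admission history.

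**The case against.** The best defence is that the article uses readmission loosely. Section 5.8 collects any subsequent hospitalisation for everyone, section 5.15 forecasts admissions, and Table 1 labels the SCRinHF dimensions as ambulatory readmission risk, so use in outpatients is the declared purpose. Section 5.7 refers outcome definitions to external clinical data standards and sends ambiguous data to a panel, with agreement of two investigators required. The study is a feasibility cohort that calls itself hypothesis generating and disclaims generalisability.

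Much of this stands, and it rules out several stronger readings that a reader might infer:

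- *That the outcome is undefined.* Hospitalisation is collected for all patients, and the cited standards cannot be checked here. What remains is that no section equates hospitalisation with the readmission named in 5.12.
- *That a never-admitted patient's first admission would be discarded.* Nothing in the text instructs this.
- *That only previously admitted patients can have a readmission, so the usable sample shrinks.* This is wrong: a patient first admitted during follow-up can be readmitted within it.
- *That the 80% criterion loses precision.* It is stated as concordance between tools, which does not depend on admission history.
- *That time since discharge biases one tool against the other.* Both are scored on the same patients.

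The defence does not reach the rest. An external definition of readmission would not add an index admission to the entry criteria, the panel is given no rule for stays before scoring, and the cited rates remain readmission rates. Eligibility, setting, outcome and window are all fixed in this document, so the mismatch is not detail left to an analysis plan.

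**Conclusion.** The concern holds, at moderate severity. The observed outcome mixes first admissions with readmissions at unspecified times after discharge, and the window in 5.7 admits events up to 6 months before recruitment and hence before the tools are scored. The readmission rates cited in the Background and section 5.15 do not describe a cohort recruited from outpatient and support services without an index admission. The forecast above 100 depends on treating all 40 as newly discharged throughout; with half so treated it is about 65 to 80, and with none about 10 to 40. Those ranges rest on an assumed 0.25 to 1.0 admissions per year in the other patients and on assumed shares, since the document gives neither. The share of the cohort affected is unknown until the baseline hospitalisation data are tabulated.

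The finding is confined to predictive validity, the readmission count and the forecast. It does not impugn the 80% concordance between tools.

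**What to change.** 1. In 5.9 and 5.12, name the observed outcome as hospitalisation, as already collected under 5.8, within 12 months after baseline tool scoring, counted the same way whatever the prior admission history. The risk category that the tools assign can keep its name.
2. Align the period of interest in 5.7 with that time zero, so that stays before scoring are baseline data only.
3. Report predictive performance descriptively by recent hospitalisation at baseline, from the data in 5.6. With about 40 patients this is a description, not a subgroup test.
4. In 5.15, restate the admission forecast with a rate for ambulatory patients, or label it as assuming recent discharge.
5. Limit the conclusion to hospitalisation risk in ambulatory patients with reduced ejection fraction.

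The cost is wording in three sections (5.7, 5.9 and 5.12), one recalculated or relabelled forecast in 5.15, and one table from data already collected. The real downside is that the study can no longer claim to predict post-discharge readmission.

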### Participant assessments

5.6.

Baseline self-reported demographics and past medical history

A self-report questionnaire supplemented by a review of the patient’s medical records will inform baseline parameters collected: (1) determining clinical stability, (2) identifying key clinical, medication-related, and social issues, (3) assessing the status of key cardiovascular and CVD-related risk factors, and (4) recent hospitalisations (NB// Medical information from cardiology interaction will be extracted from recent clinical review).

*Demography:* age, sex, marital status, social support, socioeconomic status (income), primary residence, mode of travel, and language and cultural group the patient identifies with*Behavioural factors:* smoking status, alcohol consumption, dietary behaviours, amount of physical activity, and sedentary time in the previous week*Health:* primary healthcare arrangements, co-morbidities, medications, primary care physician, pharmacy, assess to prior medical events, medical conditions/diagnoses, current treatments/medication regimes, prior hospitalisations, and procedures, with a particular focus on cardiovascular events, renal disease and diabetes, and self-reported history of hypertension, dyslipidaemia, and family history of coronary heart disease (CHD).*Clinical Assessments: will include* current symptom profile, New York Heart Association classification, height, weight, waist and hip circumference, blood pressure, cardiovascular and respiratory system assessment, and 12-lead electrocardiogram (ECG).*Psychosocial Status:* Psychosocial status will be assessed utilising standardised questionnaires, focused specifically on depression as assessed by the adapted PHQ-9 depression inventory and CFPI tool.

Biochemical assessments

Pathology tests will be undertaken by accredited laboratories with standardised reference ranges; evaluation will be on current guidelines. All tests will be recorded directly from laboratory reports to standard CRFs. Investigations undertaken at baseline, 6 and 12-month follow-up include: fasting lipid profile (total cholesterol, high-and low-density lipids, and triglycerides – mmol/L); glycosylated haemoglobin (HbA1c), urinary albumin: creatinine ratio (mmol/L), B-type natriuretic peptide (NT-proBNP), high-sensitive C-reactive protein (hs-CRP), and renal and liver function tests (serum creatinine, urea, sodium, potassium and estimated glomerular filtration rate, bilirubin, ALT, and GGT).

### Data collection and storage

5.7.

Data will be collected on a standardised case note extraction form (CRF) by trained staff. Information will be accessed by self-report questionnaire and multiple sources including hospital records, primary healthcare clinic records, specialist databases, and record systems maintained by visiting district medical officers. The period of interest for data collection will be 0–12 months following the initial commencement of SGLT2-i. Data definitions will be standardised and widely accepted case and outcome definitions as outlined in the ACC Clinical Data Standards will be used (29). A locally convened panel of the research team will review cases that demonstrate ambiguity in data definitions or outcome data, and consensus sought. Only when two investigators agree will the data be recorded. All data will be de-identified when transferred for analysis, and subsequently will be stored within locked files at the Institute/University research office.

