**Methods and analysis:**

*SELFMAN-HF* is a prospective, observational study to evaluate the feasibility and validity of the *SCRinHF* tool, a one-page self-management and readmission risk prediction tool for CHF, with an established, comprehensive CDSM tool. Eligible patients will have CHF with left ventricular ejection fraction <40% and commenced sodium glucose co-transporter-2 inhibitors (SGLT2-i) within 6 months of recruitment. The primary endpoint is the 80% concordance in readmission risk predicted by the *SCRinHF* tool. The study will recruit >40 patients and is expected to last 18 months.

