### Assessment of study data, measures, recommendations, and intervention (Phase 2)

5.3.

Details of the CFPI, heart foundation cardiovascular chronic disease tools, and patient assessment and chronic illness care satisfaction questionnaire (PACIC) are previously summarised [Table 3 in Iyngkaran et al. (3)] and published (3, 7, 8, 11). The CFPI tool and PACIC will be used to obtain information on patients’ CDSM capacity and patient satisfaction informing the CHF journey over 12 months. The PACIC is in three parts, where self-management assumes a component of the third category. Other study measures include the assessment of participants’ clinical changes in CHF and general wellbeing through the 6-month CFPI score, NYHA class, MLWF and 6MWT, and plasma NT-proBNP (Figure 3). Data on readmissions and mortality will be obtained from patient interviews and, if possible, healthcare records from main health providers, hospitals, primary healthcare (PHC) records, and community cardiac services. Cost–benefit analysis will be determined using standard billing criteria for public hospital funding Medicare Australia. These data will be compared with any ongoing prospective works on the CHF patient journey in Victoria. All enrolled patients will receive routine medical care as per Heart Foundation guidelines 2018 (27, 28). No additional investigations will be required from usual care. Comparing the long form CFPI and short form (*SCRinHF* tool) – trained staff who administer the CFPI will record the time to complete the process. The *SCRinHF* tool (Table 1) will be completed by an independent staff from those who filled in the CFPI. They are blinded to patients and will receive access to raw data on patients. The time to complete this will also be recorded.

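### Two unreconciled time zeros: data collection runs from SGLT2-i start, follow-up from recruitment up to 6 months later, and no rule keeps pre-scoring events out of the predictive analysis

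*Protocol article*

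**What the plan says.** All references are to the protocol article.

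- **Data window (5.7, Data collection and storage).** "The period of interest for data collection will be 0–12 months following the initial commencement of SGLT2-i". The same section covers extraction from hospital and primary care records, case and outcome definitions, and panel review of ambiguous outcome data.
- **Entry (Abstract; section 4).** Eligible patients have "commenced sodium glucose co-transporter-2 inhibitors (SGLT2-i) within 6 months of recruitment". Section 4 repeats the limit and excludes patients who started longer ago.
- **Follow-up (5.5).** Recruitment runs from September 2021 to September 2022, and participants are "followed for 12 months, ending September 2023". Section 5.8 then looks for hospitalisations, major events and interventions that come afterwards, at 6 and 12 months, without naming the starting point.
- **Scoring of the CFPI (5.5).** It follows consent: "Patients identified will be referred to the study case manager for consent, and thetime will then be arranged to review the CFPI, PHQ-9, MLHF, and" the PACIC.
- **Scoring of the SCRinHF (5.3).** Independent staff complete it from patient data: "They are blinded to patients and will receive access to raw data on patients". Neither a scoring date nor a data cut-off is given.
- **Baseline history (5.6).** Baseline parameters include "recent hospitalisations", and prior hospitalisations appear again under the health items.
- **Use of the events.** Predictive validity for 12-month outcomes is an aim (2.1 and section 3). One version of the primary endpoint in 5.9 is expressed in MACE and medical events. Section 5.12 lists the number of readmissions as a primary outcome.

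**The concern.** A predictive-validity analysis needs the score to be fixed before the outcome period opens. The section 5.7 clock starts at a treatment date that can precede scoring by months, so its window can contain admissions that had already happened when the tools were completed. Three things would follow if that clock governed the analysis.

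- An admission between SGLT2-i start and scoring could be known to the rater and also lie inside the outcome window.
- Patients would have unequal prospective follow-up, depending on when in the 6-month allowance they enrolled.
- The stretch before enrolment would contain no deaths, because patients must be alive to enrol. Mortality over the window would then be understated, while admissions in the same stretch could still be counted.

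Sections 5.15 and 6 say the cohort's results are to inform the size of a future controlled study, so distorted event rates would carry forward.

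**Working it through.** **Step 1. The plan's own event figures (5.15).** Inputs: 40 patients (the plan says more than 40), 25% readmission at 1 month, 25% mortality at 1 year.

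- Deaths: 40 × 0.25 = 10. With 41 patients it is 10.25, which meets the plan's bound of more than 10.
- Admissions, if the 1-month rate recurs every month: 40 × 0.25 × 12 = 120 ignoring deaths. With 25% annual mortality at a constant hazard h = −ln(0.75) = 0.2877, person-years are 40 × 0.25 / 0.2877 = 34.8, giving 34.8 × 12 × 0.25 = 104. Both meet the plan's bound of more than 100.

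**Step 2. Which clock fits the calendar.** A last patient recruited in September 2022 and followed for 12 months finishes in September 2023, the end date in 5.5. On the 5.7 clock that patient's window would close between March 2023 (lag 6 months) and September 2023 (lag 0). The end date therefore fits recruitment as time zero. Section 5.14 adds a third timing, a census of all outcome data in December 2022, and does not settle which clock governs.

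**Step 3. Overlap under a literal 5.7 window.** Let L be the months from SGLT2-i start to scoring, taking scoring to occur at recruitment, so L is 0 to 6. Pre-scoring share = L/12; prospective months = 12 − L. The documents give no distribution of L. Uniform entry over 0 to 6 months is an assumption and gives a mean of 3.

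| L (months) | Share before scoring | Prospective months | Of 100 admissions, before scoring (constant rate) |
|---|---|---|---|
| 0 | 0% | 12 | 0 |
| 1 | 8% | 11 | 8 |
| 3 (mean if uniform) | 25% | 9 | 25 |
| 6 (maximum) | 50% | 6 | 50 |

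Using 120 admissions, the last column is 0, 10, 30 and 60. At L = 6, the 12-month visit falls 18 months after SGLT2-i start, 6 months outside the 5.7 window.

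**Step 4. Sensitivity to front-loaded risk.** Suppose the 25% at 1 month and 50% at 6 months ran from SGLT2-i start. This is a strong assumption, since the Background ties those rates to discharge. A Weibull curve through both points has shape 0.49 and reaches 62% at 12 months. The share of first readmissions before scoring is then 0.50 / 0.62 = 80% at L = 6, and about 58% averaged over uniform lags.

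**Step 5. Deaths, only if collection really stopped 12 months after SGLT2-i start.** An enrolled patient can die only in the remaining 12 − L months. At the mean of 9 months: 40 × (1 − 0.75^(9/12)) = 40 × 0.194 = 7.8, against 10 over a full 12 months. Under the follow-up in 5.5 there is no such loss.

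**The case against.** The strongest reply is that 5.7 describes a period for collecting data and does not define a prediction window. Collecting records from SGLT2-i start is compatible with using the early part as history, and 5.6 does list earlier hospitalisations as baseline data. Sections 5.5 and 5.8 point to follow-up from recruitment for later events. On that reading the right data would be collected and nothing would be lost.

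Much of this stands. A reader might infer from 5.7 that events before scoring will be counted as predicted. The documents do not support that: no section says so. Equally, none excludes them, and 5.7 governs outcome definitions and review of outcome data, so its window cannot be set aside as applying to baseline data alone.

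A reader might also infer that the tools' apparent discrimination will be inflated. That is not demonstrated. The items in Table 1 do not include a count of prior admissions. A route for leakage exists, because raters see raw data with no cut-off and the chronology item scores an acute presentation, but its effect cannot be sized from the documents.

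The reach is also limited. Where the primary endpoint is concordance or correlation of readmission risk between the CFPI and the SCRinHF, moving the outcome window changes nothing.

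Finally, this is a small, hypothesis-generating feasibility cohort, and an article may leave analysis detail to a fuller document. That would excuse silence about time zero. It does not excuse stating one anchor in 5.7 and another in 5.5.

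**Conclusion.** The concern holds as an unreconciled definition. The article gives two time zeros, SGLT2-i start and recruitment, which can differ by up to 6 months, and it has no rule keeping pre-scoring events out of the predictive analysis. It does not establish that the plan counts such events as predictions.

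If 5.7 were followed literally, each patient would have 0% to 50% of the window before scoring and 6 to 12 months of prospective follow-up. The 25% average rests on uniform entry lags. The 25 in 100 admissions also needs a constant rate, and front-loaded risk would make the share larger. The drop from 10 to about 7.8 expected deaths in 40 patients needs uniform lags, 25% annual mortality and collection that stops 12 months after SGLT2-i start.

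What is exposed is predictive validity (2.1, section 3), the event-based endpoints (5.9, 5.12) and the event rates carried to a future RCT. Because the choice of clock changes which events are counted, this is more than a missing detail and should be settled before outcome data are analysed.

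**What to change.** 1. In 5.7, replace the SGLT2-i anchor with the date of the baseline CFPI/SCRinHF assessment, and use that date as time zero in 5.5, 5.8 and the event-based endpoints.
2. Count readmissions, MACE and deaths only in the 12 months after that date, with the same window for every patient.
3. Limit the raw data given to SCRinHF raters to data up to that date, whenever the form is actually completed.
4. Record admissions between SGLT2-i start and baseline as history only, and record months since SGLT2-i start as a descriptive baseline variable.
5. State how the December 2022 census in 5.14 relates to the 12-month outcome window.

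The cost is protocol and CRF wording, two dates per patient (SGLT2-i start and baseline assessment) and a dated extract for the raters. No extra follow-up is needed, since 5.5 already plans 12 months from recruitment; if the assessment falls some time after consent, the last window closes later by that interval.
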